## Methods

### Study design and objectives

RECEDE-Myelopathy is a multicentre, double-blind, randomised, placebo-controlled trial assessing the efficacy of Ibudilast as an adjuvant treatment to decompressive surgery for DCM. Participants will be randomised to receive either 60–100 mg Ibudilast (interventional arm) or placebo (control arm) starting within 10 weeks prior to surgery and continuing for 24 weeks after surgery for a maximum of 34 weeks of treatment. Preoperative treatment may leverage the effects of inhibition of PDE3, while postoperative treatment aims at regeneration-inducing effects outlined above. The primary objective will be to compare improvement in pain or physical function at 6 months after surgery between the two arms of the trial. We hypothesise that adjuvant therapy with Ibudilast leads to a meaningful and additional improvement in either pain or function, as compared with standard routine care (decompressive surgery). Planned start date for study recruitment is September 2021, with planned end being September 2025.

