### Adaptive sample size design

The minimum clinically important difference (MCID) for the mJOA is estimated to be between 1 and 2 points.^67^ Although not exclusively validated for DCM, the MCID for VAS neck and VAS arm pain has been calculated for degenerative disease of the cervical spine with values ranging from 8 to 26 mm.^64 65^ Both VAS pain and mJOA improve more than the MCID with surgery alone,^57^ and the amount of change is linked to the pre-operative baseline.^67^ Consequently, in consensus with patients we have determined the MCID of the VAS pain score as being 1 cm and for the mJOA 1 point. This has been modelled to ensure statistical power across all baseline scenarios.

On this basis, a total sample size of 362 participants under equal randomisation will provide 85% power to detect a difference of 1 between treatment arms on the mJOA scale (assuming a SD of 2.89), using a two-sided t-test at a 2.5% significance level to adjust for multiple comparisons.^68^ The trial is also powered to detect a similar difference on the VAS neck pain scale (assuming a difference of 1 and a SD of 2.88).

A blinded interim analysis will be conducted to refine the power calculation. The aim will be to reassess the sample size in time to allow any potential extension and increase in sample size to be put into effect. Reduction in sample size will not be permitted. Any sample size increase will be based on checking the assumption regarding the SD, and will not estimate any treatment effect, hence no subsequent adjustment to future analyses is needed.

Under such a framework, the theoretical optimal time to schedule such an interim analysis would be just as the last patient is recruited under the original sample size (n=362) following which a decision could be taken to either halt or extend recruitment. However, for reasons of practicality a window for the interim analysis will be up to a period of 4 months before reaching the total sample size.

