The SD and correlation of both endpoints will be reassessed using data pooled across the arms. The three possible statistically significant conclusions of the formal hypothesis testing (VAS; mJOA; both) will be provided with revised target sample sizes needed to achieve 85% power under the same MCID values, but with revised estimates for the SD values and correlation. A recommended revised sample size will be the smallest of the three new target sample sizes or the original sample size if this is larger; hence the recommended sample size will never be a reduction from the original.

The next step of the interim analysis will be to calculate the conditional power of the three possible positive outcomes based on, the estimated unblinded treatment effects from the current data, plus, the distribution of future data from the revised sample size under the corresponding combinations of true treatment effects (MCID or zero), and SD and correlation estimates from the first step. If all three conditional power values are <30% then the recommendation would be to halt the study.

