### Statistical methods

The primary endpoint and key secondary endpoints are all measured on a continuous scale. A comparison of mean values between treatment arms, adjusting for baseline covariates, will be provided using linear regression. Estimates, standard errors, 95% CIs and p values will be provided.

For formal hypothesis testing, a closed testing approach will be used to deal with multiple endpoints.^70^ Initially either of the coprimary endpoints (mJOA or VAS neck pain) may test a null hypothesis of 0 mean difference at a two-sided 2.5% significance level,^71^ with the remaining primary endpoint tested at 5% significance level. This will enable us to determine whether the study drug is effective on pain or function independently.

Subsequently a gate-keeping approach will be used where an endpoint below the primary endpoint in the prespecified ordering is only tested if all the preceding endpoints reject the null hypothesis, using the nominal p value. If an endpoint does not reject the null, then all endpoints below it have the same conclusion, not rejecting the null, regardless of their nominal p value. The ordering is, after primary endpoints, Short Form Survey (SF-36) Physical Component Summary (PCS) and then SF-36 Mental Component Summary (MCS).

Secondary endpoints will be compared between treatment arms using approach regression techniques: linear regression for continuous endpoints, logistic regression for binary endpoints, and Cox regression for time-to-event.

The following baseline covariates, in addition to the baseline value of the endpoint, will be used to adjust all comparisons

Time to onsetSmoking status (yes/no)AgePsychiatric comorbidities (yes/no)Impaired gait (yes/no)

A detailed statistical analysis plan will be produced before the final database lock.

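### The futility recommendation checks VAS, mJOA and both against 30% one at a time, and never checks the chance of at least one significant co-primary, which is the event that meets the trial's objective

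*Protocol article*

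**What the plan says.** Under Adaptive sample size design, the protocol article takes "The three possible statistically significant conclusions of the formal hypothesis testing (VAS; mJOA; both") and uses them twice. They first serve to re-estimate the sample size. They then serve to compute conditional power from the interim effects, with future data generated under the matching combination of true effects, each either the MCID (1 mJOA point, 1 cm VAS) or zero. The stopping guidance is "If all three conditional power values are <30% then the recommendation would be to halt the study".

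Under Study design and objectives, "The primary objective will be to compare improvement in pain or physical function at 6 months after surgery", and the hypothesis there and in the Abstract is improvement in one or the other. Under Statistical methods, either co-primary may be rejected first at a two-sided 2.5% level, "with the remaining primary endpoint tested at 5% significance level". One rejection is therefore a positive result.

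**The concern.** The 30% threshold is applied to each endpoint as if it were the only active one, and to the joint win. It is never applied to the union, which is the probability that the trial meets its objective. The gap is widest when both endpoints lean moderately in the drug's favour. The article's rationale, a drug suited to both pain and function, predicts that pattern. A committee told that all three values are below 30% would naturally take the chance of a positive trial to be below 30%. On the rule's own assumptions it may not be.

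**Working it through.** **Inputs from the article.** For mJOA, the article states that "a total sample size of 362 participants under equal randomisation will provide 85% power to detect a difference of 1 between treatment arms". Its variability input for that endpoint reads "assuming a SD of 2.89", and its planned comparison is described as "using a two-sided t-test at a 2.5% significance level to adjust for multiple comparisons". For VAS neck pain the inputs are given as "assuming a difference of 1 and a SD of 2.88". The closed test uses critical values 2.241 (2.5%) and then 1.960 (5%).

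**Inputs assumed.**
- The correlation of the endpoints in the direction of benefit is not given; range 0 to 0.7.
- The share of outcome data at the interim is not given. Taking even accrual over the 48 months from September 2021 to September 2025, and an outcome about 8.3 months after randomisation (up to 10 weeks before surgery plus 6 months after), an interim 4 months before full accrual has (44 − 8.3)/48 = 0.744 of the data, about 269 participants. At full accrual it has (48 − 8.3)/48 = 0.827. A wider range of 0.50 to 0.90 was also run.
- The sample size stays at 362. The matching combinations are read as MCID on one endpoint and zero on the other for a single win, and MCID on both for the joint win.

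**Step 1, the plan's own figure.** The standardised effect is θ = 1/(2.89 × √(4/362)) = 3.292. The noncentral t gives 85.06% power for mJOA at N = 362, and 85.3% for VAS. The stated sample size is reproduced.

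**Step 2, the boundary.** With interim statistic z and data fraction t, the final statistic is √t·z + (1 − t)·θ + √(1 − t)·e, with e standard normal. At t = 0.744 this is 0.863z + 0.843 + 0.506e. Conditional power at the 2.5% level equals 0.30 when (2.241 − 0.843 − 0.863z)/0.506 = 0.524, so z is about 1.31. That is an observed difference of about 0.46 (points or cm), nominal p about 0.19.

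**Step 3, at least one win.** Put both endpoints at that boundary with both future effects at the MCID. Then P(at least one) = 0.30 + 0.30 − P(both exceed 2.241). At correlation 0 this is 0.60 − 0.09 = 0.51.

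| Correlation | At least one | Both (closed test) |
|---|---|---|
| 0 | 0.51 | 0.22 |
| 0.3 | 0.47 | 0.26 |
| 0.5 | 0.44 | 0.29 |

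Counting step-down wins in the single-endpoint values moves the boundary slightly and gives 0.505, 0.468 and 0.440. At correlation 0.7 the joint value is 0.32 at this point, so the rule does not halt there; lowering both trends until it does leaves 0.38 to 0.40 (t = 0.65 to 0.75). Over t = 0.50 to 0.90 and correlation 0 to 0.7, the boundary value runs from 0.34 to 0.51.

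**Step 4, how quickly it falls.**
- If the second endpoint's conditional power is 10% instead of 30%, at least one is 0.34 to 0.37.
- If only one endpoint has the MCID in future data, it is about 0.28 to 0.31 (t = 0.65 to 0.75).
- If future data follow the observed trend, it is about 0.06 to 0.15 (t = 0.65 to 0.75).

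**Step 5, other readings of the three values.** If they are mutually exclusive (VAS only, mJOA only, both), the boundary value is about 0.42 to 0.48. If all three assume the MCID on both endpoints, it is about 0.34 to 0.45. Both remain above 0.30.

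**Step 6, how often it matters (simulation).** With the MCID true on both endpoints and 74% of the data, 39%, 26% and 20% of halts (correlation 0, 0.3, 0.5) occur with the chance of at least one win at or above 30%. At 83% of the data the share is 15 to 25% (correlation 0.3 and 0). Such halts are rare: over t = 0.65 to 0.75, 0.2 to 1.7% of trials halt, and the whole rule costs 0.2 to 0.4 percentage points of power at most (for example 96.1% to 95.9%). At half the MCID it costs under 1 point. Adding the union recovers about 0.1 points at the full MCID and 0.2 to 0.3 points at 50 to 70% of it.

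**The case against.** A reader might infer that a trial halted under this rule still has a 45 to 50% chance of success. The documents do not support that. The figure needs both endpoints just under the boundary together, low to moderate correlation, and the full MCID on both endpoints in the remaining patients, when the interim shows under half of it. With the MCID true on both and 74% of the data, the chance reaches 0.44 in only 3.7% (correlation 0) or 0.9% (correlation 0.3) of halts, roughly 1 to 1.5 trials in 10,000. Averaged over halted trials, the true chance is 17 to 27% at the full MCID and 3 to 4% at half of it. This part of the objection stands.

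A reader might also infer that the joint value is redundant. It is not: on the symmetric boundary it reaches 0.32 at correlation 0.7 with 74% of the data, and 0.32 to 0.34 at correlation 0.5 to 0.7 with 83%. There it prevents a halt.

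It can further be said that the design is powered for each endpoint separately, that continuing while any one designed conclusion is reachable is coherent, and that the rule yields only a recommendation in a trial overseen by an independent data monitoring committee and a steering committee. All true, and reasons for low severity. But the objective and the closed test count a single win as success, and MCID in future data is the rule's own convention, so the union on that convention is a fair quantity to hold against 30%.

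**Conclusion.** The point holds as one of coherence, not of lost power. The rule does not compare the probability of meeting the objective with its own threshold. At the extreme, it can recommend halting when that probability, on its own MCID convention, is about 0.44 to 0.51. This rests on an assumed correlation of 0 to 0.5 and about 74% of outcome data at the interim; the other readings and fractions examined give lower boundary values, all still above 0.30. The effect on overall power is a few tenths of a percentage point. Low severity, worth correcting because it is cheap.

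**What to change.** In Adaptive sample size design, keep the three existing conditional powers and add a fourth: the conditional power of rejecting at least one co-primary null by the same closed test, with both future effects at the MCID and the interim SDs and correlation. Recommend halting only if this fourth value is also below 30%. State which true effects are assumed for each of the four values.

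Cost: one sentence and one more probability from the same bivariate calculation, with no patients and no extra unblinding. At about 74% of the data, the trial would halt about 1 percentage point less often under no effect (where roughly 83 to 85% of trials halt at t = 0.75) and 2 to 3 points less often at half the MCID (where roughly 21 to 30% halt).

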### Trial monitoring

All data collected during the trial will be recorded into a Case Report Form (CRF), which will be labelled using a participant’s unique trial ID and date of birth. CRFs will be completed by the local research team and copies will be sent to trial coordination centre, where it will be entered into a central digital database. Safety assessments will be conducted by local investigators and reported and handled according to a predefined trial protocol. This includes a mechanism to capture surgical complications.^69^ The Trial Steering Committee (TSC) will provide overall supervision with respect to the conduct of the trial. The TSC will consist of an independent Chairperson ([name]), a PPI representative ([name]), independent clinical and science experts ([name] and [name]), clinical pharmacology and neurosurgery experts ([name] and [name]), the Chief Investigator and members of the Trial Management Group (eg, trial statistician, trial manager). The ethical and safety aspects of the trial will be overseen by an independent Data Monitoring Committee (DMC) who will meet once a year and their meetings will be timed so that reports can be fed into the TSC meetings. Safety assessment will be performed for every participant since consent and until end of their participation in the trial. To date, there are no known expected serious adverse reactions (SARs) for Ibudilast, and thus any reported SAR will be considered a suspected unexpected serious adverse reaction. Furthermore, surgical complications will be followed up as events of special interest to be reviewed by the DMC.

### Statistical methods

The primary endpoint and key secondary endpoints are all measured on a continuous scale. A comparison of mean values between treatment arms, adjusting for baseline covariates, will be provided using linear regression. Estimates, standard errors, 95% CIs and p values will be provided.

For formal hypothesis testing, a closed testing approach will be used to deal with multiple endpoints.^70^ Initially either of the coprimary endpoints (mJOA or VAS neck pain) may test a null hypothesis of 0 mean difference at a two-sided 2.5% significance level,^71^ with the remaining primary endpoint tested at 5% significance level. This will enable us to determine whether the study drug is effective on pain or function independently.

Subsequently a gate-keeping approach will be used where an endpoint below the primary endpoint in the prespecified ordering is only tested if all the preceding endpoints reject the null hypothesis, using the nominal p value. If an endpoint does not reject the null, then all endpoints below it have the same conclusion, not rejecting the null, regardless of their nominal p value. The ordering is, after primary endpoints, Short Form Survey (SF-36) Physical Component Summary (PCS) and then SF-36 Mental Component Summary (MCS).

Secondary endpoints will be compared between treatment arms using approach regression techniques: linear regression for continuous endpoints, logistic regression for binary endpoints, and Cox regression for time-to-event.

The following baseline covariates, in addition to the baseline value of the endpoint, will be used to adjust all comparisons

Time to onsetSmoking status (yes/no)AgePsychiatric comorbidities (yes/no)Impaired gait (yes/no)

A detailed statistical analysis plan will be produced before the final database lock.

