### Enrolment and randomisation

Those patients who satisfy the screening criteria and agree to study participation are enrolled and randomised at 1:1 to one of the two treatment arms. A web-based randomisation system (sealed envelope) performing stratified blocked randomisation will be used stratifying by baseline mJOA (<12 vs ≥12), age (<60 years vs ≥60 years) and time to onset of the disease (>6 months vs ≤6 months); random block size will be used. Throughout randomisation and follow-up, the subjects, physicians and data collectors remain blinded to group allocation.

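### Baseline mJOA is a stratification factor but is left out of every model whose endpoint is not mJOA, including co-primary VAS neck pain: a small, conservative loss that can be removed at no cost

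*Protocol article*

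**What the plan says.** Enrolment and randomisation describes stratified blocked 1:1 allocation, "stratifying by baseline mJOA (<12 vs ≥12), age (<60 years vs ≥60 years) and time to onset of the disease", the last split at 6 months.

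Statistical methods sets the model: "A comparison of mean values between treatment arms, adjusting for baseline covariates, will be provided using linear regression". It then fixes the adjustment set: "The following baseline covariates, in addition to the baseline value of the endpoint, will be used to adjust all comparisons". Five covariates follow: time to onset, smoking status, age, psychiatric comorbidities and impaired gait.

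On testing, the same section says: "Initially either of the coprimary endpoints (mJOA or VAS neck pain) may test a null hypothesis of 0 mean difference at a two-sided 2.5% significance" level. The remaining co-primary is then tested at 5%. SF-36 PCS and SF-36 MCS follow in order, each tested only if everything before it has rejected.

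Setting the three stratification factors against the models:

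| Stratification factor | mJOA model | VAS neck pain model | SF-36 PCS and MCS models |
|---|---|---|---|
| Age | yes | yes | yes |
| Time to onset | yes | yes | yes |
| Baseline mJOA | yes, as the endpoint's own baseline | no | no |

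The same gap applies to every other secondary endpoint that is not mJOA. The article gives no reason for it.

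**The concern.** Stratified randomisation balances the arms on the stratifying factor. If that factor predicts the outcome, the treatment difference varies less from trial to trial than it would under simple randomisation. A model without the factor leaves its contribution in the residual variance and so reports a standard error that is too large. Confidence intervals are then too wide, the test runs below its nominal level, and some power is lost.

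VAS neck pain is one of two co-primaries, so a missed rejection there has consequences further on: it denies mJOA the 5% level if mJOA has not rejected at 2.5%, and it closes the gate to both SF-36 tests. Two of the three stratification factors are in every model, so the absence of the third looks like an oversight. Including the endpoint's own baseline covers mJOA for one endpoint only.

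**Working it through.** **Inputs from the article** (Adaptive sample size design; Statistical methods): N = 362, so 181 per arm; difference 1; SD 2.89 for mJOA and 2.88 for VAS neck pain; two-sided t-test at 2.5%; 85% power.

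**Assumption:** the partial correlation r between the mJOA stratum and 6-month VAS, given the other covariates. The article does not give it, so 0.1, 0.2 and 0.3 are shown.

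**Step 1: reproduce the plan's figure.** Noncentrality = 1 / (SD × √(2/181)); critical t on 360 df = 2.251.
- mJOA: 1 / (2.89 × 0.1051) = 3.292, power 85.1%. The smallest n reaching 85% is 181 per arm, so 362 reproduces.
- VAS: 1 / (2.88 × 0.1051) = 3.303, power 85.3%.

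**Step 2: standard errors.** Reported SE with mJOA omitted: 2.88 × √(2/181) = 0.3027. True SE when the factor is balanced: 0.3027 × √(1 − r²).

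**Step 3: true level with mJOA omitted.** 2 × [1 − Φ(2.2414 / √(1 − r²))].

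**Step 4: power.** Stratification reduces the true SE whether or not the model contains the factor, so both versions share the noncentrality 1 / true SE. They differ only in the critical value: 2.251 / √(1 − r²) with the factor omitted, and 2.251 with it included.

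| r | True SE | Reported / true SE | True level, omitted | Power, omitted | Power, included | Loss (points) |
|---|---|---|---|---|---|---|
| 0.1 | 0.3012 | 1.005 | 2.43% | 85.4% | 85.7% | 0.3 |
| 0.2 | 0.2966 | 1.021 | 2.22% | 85.8% | 86.8% | 1.0 |
| 0.3 | 0.2888 | 1.048 | 1.88% | 86.4% | 88.7% | 2.2 |

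Losses are taken before rounding.

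**Step 5: simulation check.** Eight equal strata, permuted blocks of 4 and 6 (assumed sizes), 362 participants, normal critical values, 20,000 runs under the null and 8,000 with a difference of 1. With the stratum explaining 10% of the variance (r about 0.32), the level was 1.90% omitted and 2.46% included; power was 86.8% and 89.2%. At 5% (r about 0.22), the level was 2.10% and 2.50%; power was 86.6% and 87.6%. Direction and size agree with the table.

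**Step 6: sensitivity to two simplifications.**
- *r refers to the continuous score.* Only the <12/≥12 split is balanced. If the split carries 64% of the score's variance (an assumption: median split of a normal variable), replace r² by 0.64r² in step 3. The level becomes 2.45%, 2.32% and 2.10%.
- *2.88 is an unadjusted SD.* If baseline VAS and the five listed covariates jointly correlate 0.5 with the outcome (an assumption), the residual SD is 2.88 × √0.75 = 2.494 and the reported SE is 0.2622. By normal approximation, power omitted is Φ((1 − 2.2414 × 0.2622) / (0.2622 × √(1 − r²))) = 94.3%, 94.6% and 95.0%. Power included is Φ(1 / (0.2622 × √(1 − r²)) − 2.2414) = 94.4%, 95.1% and 96.1%. The loss shrinks to about 0.1, 0.5 and 1.0 points.

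No figure can be given for SF-36 PCS or MCS, because the article states neither an effect size nor an SD for them.

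**The case against.** **The harm is conditional and may be slight.** It arises only if baseline mJOA predicts 6-month neck pain after baseline VAS, age, time to onset and impaired gait are accounted for. The article gives no such association, and its Discussion says that mJOA does not capture pain. The sample size section does link the amount of change in pain and mJOA to the preoperative baseline, but does not say whose baseline. Impaired gait may also carry part of the mJOA information. This stands: the omission is certain, its cost is not, and the lower end of the range is more likely.

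**The list may not be exhaustive, and a detailed statistical analysis plan is promised.** This carries little weight. The article does not leave the covariates open; it names them for all comparisons. A later plan that follows the list repeats the gap, and one that departs from it must change the published wording.

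**Stronger readings the documents do not support.** A reader might infer that the VAS test is invalid or biased. It is not: the error makes the test conservative, so a positive result is safe. A reader might infer that the trial is undersized. It is not: N = 362 comes from an unadjusted t-test and reproduces. A reader might also measure the loss against the planned 85.3%, which gives 0.4, 1.5 and 3.4 points (85.7, 86.8 and 88.7 less 85.3). That overstates it, because stratification lowers the true variance even when the model ignores the factor; the proper comparator is 85.4%, 85.8% or 86.4%.

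**Conclusion.** The point holds as a minor one. A factor used to stratify randomisation is missing from the co-primary VAS neck pain model, from both gate-kept SF-36 models and from all other non-mJOA comparisons. For VAS, with assumed partial r from 0.1 to 0.3 and SD 2.88, the cost is a true level of about 2.4% to 1.9% at nominal 2.5%, and about 0.3 to 2.2 points of power. It is smaller still if the other covariates explain much of the outcome. On the level alone, the effect is also smaller if r describes the continuous score and not the stratum. The SF-36 consequence has the same direction but cannot be sized from the article.

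**What to change.** Before unblinding, add baseline mJOA to the covariate list for all comparisons, either as the <12/≥12 stratum or as the continuous score, and state which. All three stratification factors are then in every model. The mJOA model already contains it as the endpoint's own baseline.

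The cost is one line of wording and one degree of freedom out of about 360. No new data are needed: mJOA is mandatory at screening and required for eligibility. The sample size does not change. The change should be prespecified, because adding the covariate after unblinding could look data-driven.
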